**Exploratory endpoints**	
Biliary microbiome	Specific signatures of the biliary microbiome from biliary aspirate
Extent of bile duct damage	Extent of bile duct damage at 6-month MRCP compared to baseline as determined by central radiology reading

Survival is part of the primary endpoint because it is the most relevant endpoint and SSC–CIP is associated with significant mortality [2–4, 7, 9]. Liver transplantation is included as it is one treatment option that can restore liver function and avert death in advanced SSC–CIP functionally curing the disease [10]. Cholangiosepsis as systemic complication of cholangitis is a main trigger in the progress of the disease. Cholangiosepsis is promoted by bile duct stenoses which lead to deterioration of normal bile flow. Biliary complications and cholangiosepsis are frequent observations in SSC [6, 9]. In PSC, it has been shown that regular/scheduled endoscopic therapy of bile duct stenoses may lead to a reduction of cholangitis/cholangiosepsis and a prolonged transplant-free survival [11].

Cholangiosepsis can clearly be defined by SEPIS-3-criteria [12] and diagnosis of acute cholangitis according to the Tokyo Guidelines [13].

The SEPSIS-3 criteria validate sepsis based on an increase in the Sequential [Sepsis-related] Organ Failure Assessment (SOFA) score of 2 points or more, which is associated with an in-hospital mortality greater than 10%. The SOFA score [14] is obtained by assessing the following items:Respiration: PaO_2_/FiO_2_ (mmHg or kPa)Coagulation: platelets (× 10.3/μl)Liver: bilirubin (mg/dl or μmol/l)Cardiovascular: mean arterial pressure (MAP) and necessity of inotropes and/or vasopressorsCentral nervous system: Glasgow Coma Scale (GCS) [15]Renal: creatinine (mg/dl or μmol/l)

Because of preexisting organ dysfunction in the setting of secondary sclerosing cholangitis, the SOFA score will be assessed based on an increase of the SOFA score from baseline or the last study visit according to the SEPSIS-3 criteria.

Acute cholangitis is diagnosed according to the criteria of the 2018 Tokyo Guideline. For this purpose, signs of systemic inflammation, signs of existing cholestasis, and characteristic imaging are added. The diagnosis is considered confirmed when all criteria are met [13]. In detail, the following parameters are taken into account:(A) Systemic inflammation: fever and/or chills, abnormal white blood cell counts, increase of serum C-reactive protein levels, and other changes indicating inflammation(B) Cholestasis: jaundice, increased serum AP, GGT, AST, and ALT levels(C) Imaging findings: biliary dilatation, evidence of the etiology on imaging (stricture, stone, stent, etc.)

The diagnosis of acute cholangitis is definite in the presence of one item in A, one item in B, and one item in C. The diagnosis of acute cholangitis is suspected in presence of one item in A + one item in either B or C.

We therefore use the following definition of cholangiosepsis: cholangiosepsis = both parameters present:(1) Increase in SOFA score ≥ 2 points from baseline or last regular study-visit following SEPSIS 3 criteria.AND(2) Diagnosis of acute cholangitis according to the Tokyo Guidelines as seen above.

##### Secondary endpoints

The following secondary endpoints will be analyzed (Table 1):Single components of the primary endpointLaboratory parameters as change from baselineModel for end-stage liver disease score (MELD) as change from baselineUnplanned hospital admissionsUnplanned Intensive care unit (ICU) admissionsNecessity of anti-infective treatment

##### Safety endpoints

A serious adverse event (SAE) is defined as any event that is potentially life threatening and may or may not be associated with the procedure under investigation. In detail, all following events are categorized as SAEs (Table 1):DeathLiver transplantationCholangiosepsisCholangiosepsis-associated septic shockAcute on chronic liver failure (ACLF) of any gradeUnexpected in-patient hospitalization or prolongation of existing hospitalizationUnexpected ICU hospitalizationERC related SAEsOther potentially life-threatening events as assessed by the individual investigator

SAEs will be collected throughout the study and documented in the eCRF and on an SAE-form. The assessment of possible serious adverse events takes place by the investigator from inclusion of subjects into the study until the end of follow-up. SAEs including a risk–benefit evaluation of the study by the responsible investigator will be reported periodically (every 3 months) to the Ethics Committee according to the Declaration of Helsinki.

Given the profound severity of disease in the patients under investigation (hospitalized patients, mostly under critical care, multiple clinical, and laboratory abnormalities), adverse events (AEs), not fulfilling the definition of a SAEs (see above), will not be reported in this study.

#### Exploratory endpoints

As exploratory endpoints, specific signatures in the biliary microbiome and the extent of bile duct damage at 6-month MRCP compared to baseline (as determined by central radiology reading) will be analyzed.

#### Participant timeline

A time schedule of enrolment, interventions, assessments, and visits (SPIRIT figure) for participants is given as a schematic table (Table 2).

**Table 2 Tab2:** Schedule of enrollment, interventions and assessments (SPIRIT figure)

Study phase	Screening	Baseline^a^	Treatment			Follow-up
**Visit procedures**	**SCR** Day − 28 to day 0	**V1** Day 1 (diagnosis SSC)	**V2** Week 8 ± 5 days	**V3** Week 16 ± 5 days	**V4/UN/ET** Week 24 (end of treatment) ± 5 days	**FU1-FU3** Every 8 weeks ± 5 days
**Clinical assessment**						
Informed consent	x					
Eligibility criteria	x					
Gender and age	x					
Medical history	x					
ICU related history	x					
Vital signs and oxygen saturation	x	x	x	x	x	x
Height and skin color	x					
Weight	x	x	x	x	x	x
Concomitant medication	x	x	x	x	x	x
Pregnancy prevention counseling	x	x	x	x	x	
Endoscopic evaluation (ERC)		x	x (intervention group)	x (intervention group)	x (intervention group or clinically necessary for UN/ET)	
MRCP^b^	x				x	
Endoscopic intervention (ERC)		x (endoscopic evaluation only at non-intervention group)	x (intervention group)	x (intervention group)	x (intervention group or clinically necessary for UN/ET)	
Randomization		x				
Checking the components of the primary endpoint^c^			x	x	x	x
Secondary endpoints^d^					x	
SOFA score		x	x	x	x	x
Serious adverse events		x	x	x	x	x
**Laboratory assessment**						
Hematology	x	x	x	x	x	x
Serum chemistry	x	x	x	x	x	x
Thyroid function test	x					
Serum or urine ß-hCG pregnancy testing^e^	x	x	x	x	x	
Genetic sample	x					
Serum/plasma	x	x	x	x	x	x
Bile specimen		x	x (intervention group)	x (intervention group)	x (intervention group or clinically necessary for UN/ET)	

^a^Baseline/day 1 assessments must be performed prior to treatment

^b^MRCP at screening if possible. MRCP at visit 4 may only be performed if MRCP has been conducted during screening (not for unscheduled visit (UN), preferably prior to ERC)

^c^The primary endpoint is defined as occurrence of death or necessity of liver transplantation or occurrence of cholangiosepsis, whatever occurs first

^d^Secondary endpoints: single components of the primary endpoint: liver transplantation, death, cholangiosepsis; Laboratory parameters (bilirubin, AP, GGT, AST, ALT, LDH, GLDH, creatinine, CRP, CHE) as change from baseline; model for end-stage liver disease score (MELD) score as change from baseline; unplanned hospital admissions (necessity and days free of hospital care within 6 months); unplanned intensive care unit (ICU) admissions (necessity and days free of intensive care unit care, invasive ventilation, renal replacement therapy, vasopressors within 6 months), necessity of anti-infective treatment

^e^Serum pregnancy testing at screening and urine pregnancy testing during the study for females of childbearing potential only (if urine pregnancy testing is positive, a confirmation with serum pregnancy testing is required)

#### Sample size

The primary aim of the study is to demonstrate superiority of the experimental group compared to the control group in patients with SSC–CIP. The primary endpoint is a failure rate defined as a composite endpoint including liver transplantation, death, or cholangiosepsis after 6 months. Sample size calculation was conducted using a two-group continuity corrected chi-square test in nQuery Advisor 7.0. The type I error is set to 5% (two-sided) and the study aims for a power of 80%. In the present trial, a rate of 70% regarding the composite endpoint is expected in the control group. This assumption is based on the following observations: prognosis of SSC–CIP is dismal with an estimated survival of less than 50% of patients who develop SSC–CIP within 3–6 months [2, 4, 7]. The transplant-free survival of SSC–CIP differs between publications. However, in our large cohort, transplant-free survival was 38.9% at 6 months [9, 16]. Additionally, biliary complications in SSC–CIP are numerous affecting up to 90% of patients [6]. Cholangiosepsis accounts for 20–33% of these biliary complications [6]. A total reduction of 30% is assumed for sample size calculation. This number is estimated from clinical observation and experience of patients with SSC–CIP and PSC [11]. To demonstrate a reduction of the rate from 70 to 40% in the experimental group, a sample size of 49 patients per group is needed leading to *n* = 98 in total. The expected drop-out rate is assumed to be 5% (estimation from clinical practice), which leads to a sample size of 52 patients per study arm and 104 patients in total.

#### Recruitment

SSC–CIP is characterized by a grim prognosis without established diagnostic or therapeutic algorithms. From the clinical experience of the investigators, patients and their legal representatives are highly motivated and show a strong adherence to therapy and schedules due to the severity of the disease. As liver transplantation is the only validated treatment option for these patients’ referral to and treatment in tertiary care centers is of main importance [8], therefore, we expect that the number of loss to follow-up is negligible. All attempts will be undertaken to collect the information about the primary endpoint for patients that did drop-out from the study or were withdrawn. Informed consent will already address the option to contact the patient for follow-up investigations after termination of the observational period of the initial clinical trial. Nevertheless, patients where the information on the primary endpoint is not available at month 6 will be counted as treatment failures.

#### Assignment of interventions: allocation

As screening tool, patients that are suspected to have SSC–CIP by medical history, laboratory results, and sonography will undergo non-invasive imaging by magnetic resonance cholangiopancreatography (MRCP) first (Table 2). Bile duct changes in SSC–CIP will be assessed by means of MRCP at screening and visit 4. Completion of MRCP requires that all of the inclusion criteria and none of the exclusion criteria are fulfilled and that the patient has no contraindications to undergo magnetic resonance imaging (MRI). MRCP at visit 4 may only be performed if MRCP has been conducted during screening. As there are currently no technical specifications on how to perform MRCP in SSC, acquisition parameters and quality assurance should be according to existing recommendations for patients with primary sclerosing cholangitis (PSC) [17, 18]. Datasets will be sent to the Study Center in the Department of Diagnostic and Interventional Radiology of Hannover Medical School for central reading and quality assurance. As there are currently no reporting standards for SSC, image interpretation and reporting will be based on recommendations for patients with PSC [19].

Only if MRCP confirms morphologic biliary changes consistent with a high suspicion for SSC–CIP, patients will undergo consequent diagnostic ERC evaluation. Randomization will be made following definitive diagnosis of SSC–CIP via diagnostic ERC. After cannulation of the biliary system with a small ERC catheter (5F, 1.7 mm diameter), the contrast agent will be injected, and in case of typical findings of SSC (irregular bile duct system with contrast filling defects, stenoses, and prestenotic bile duct dilation), patients will be randomized. In patients randomized in the control arm, no further intervention will be performed at this point.

Permuted block randomization with variable block length stratified by center will be used to allocate patients to both study arms. Only the statistician and the unblinded data manager will have access to the randomization list. The allocation is performed via the eCRF system. Only after the patient has been documented with inclusion and exclusion criteria in the eCRF by the study site, the allocation of the patient to a treatment group will be displayed in the eCRF automatically according to the sequence determined by the randomization list. For the study sites, it is not possible to see the randomization list.

#### Data collection and management

All study data will be collected by the investigator and/or other study personnel. A clinical trial data base is provided, in which the data are entered via an eCRF. Authorized and trained staff of the study sites will enter the data in the eCRF. SAEs will additionally be documented electronically. Verification of the data in the eCRF occurs by monitoring as well as via range, validity, and consistency checks programmed in the system. Additionally, manual queries can be raised in the system by authorized study staff if further discrepancies are detected. Based on the queries, the investigator can review and answer the found discrepancies directly in the system. All changes of data entered in the eCRF can be followed by an audit trail. A quality control will be performed before the database is closed. This procedure is documented. Finally, data transfer takes place for statistical evaluation. The data management plan contains further details about data management processes.

All study staff has to give due consideration to data protection and medical confidentiality. The collection, transfer, storage, and analysis of personal study-related data are performed pseudonymized according to national regulations. The declaration of data protection is contained within the patient information/informed consent form.

An independent data safety monitoring board (DSMB) will be implemented to detect possible harms and to assure continuous risk/benefit assessment. The DSMB is a group of independent experts external to the clinical investigation assessing the progress, safety data, and, if needed, critical efficacy endpoints. Details of the definition of DSMB, its composition, and its roles and responsibilities will be set forth in a separate DSMB charter.

#### Collection and storage of biomaterial

A bile specimen of up to 5 ml will be collected at baseline and visit 2 to visit 4 (only intervention-group) to analyze the microbial microenvironment in the biliary system and bile to gain insights in its role during SSC–CIP. Moreover, blood samples per visit of approx. 15 ml (serum/plasma) and 2.6 ml (genetic analysis, only Screening) will be obtained for the evaluation of further exploratory endpoints. Details regarding the collection, processing, storage, and shipment of samples will be included in an additional lab manual. In short, specimens will be stored at − 80° C and will be shipped for central analysis to Hannover Medical School. Additional written informed consent of patients or relatives will be obtained prior to collecting biomaterial.

### Statistical methods

#### Analysis of the primary endpoint

The primary aim of the study is to demonstrate that programmed endoscopic therapy (experimental group) compared to a conservative strategy (control group) reduces the occurrence of treatment failures defined as death or necessity of liver transplantation or development of cholangiosepsis 6 months after randomization.

The primary analysis will be performed according the intention-to-treat (ITT) principle. Specifically, all patients will be analyzed as randomized. The occurrence of the primary endpoint until month 6 will be analyzed by a stratified Mantel–Haenszel estimate for the risk difference (experimental minus control group) with center as stratification factor. If the upper bound of the corresponding 95% confidence interval is below 0, superiority of the experimental group will be concluded. Missing values for the primary endpoint will be counted as treatment failures. Sensitivity analyses will be carried out in the per-protocol population, which consists of all patients who complete the study in accordance to the protocol. According to this, the primary estimand is defined as described in Table 3.

**Table 3 Tab3:** Analysis of the primary endpoint

**Objective:** Demonstrate superiority of programmed endoscopic therapy compared to standard of care on the composite endpoint of all-cause mortality, liver transplantation and cholangiosepsis 6 months after randomization	
**Target population:** Adult patients with by ERC confirmed SSC–CIP	
**Variable/endpoint:** Occurrence of any of the events	

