### Trial design

This is a multicenter, randomized, controlled parallel group trial. Patients with confirmed SSC–CIP will be randomized 1:1 either in the intervention group which will undergo scheduled invasive evaluation of the biliary tract with ERC with biliary interventions (i.e., therapeutic ERC) every 8 weeks for 6 months or in the control group which will receive non-interventional standard of care (SOC) (Fig. 1). The primary endpoint is a composite endpoint consisting of the individual components cholangiosepsis, liver transplantation, and death (whatever occurs first). Study participants will be followed up to 12 months following study inclusion. This study is an investigator-initiated trial funded by the German Research Foundation (DFG, VO 2458/1–1).

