Endoscopic evaluation has to be performed at baseline in both groups and during each ERC in the intervention group. Furthermore, an assessment of the biliary tract has to be made in each patient during V1 after diagnosis of SSC and before randomization to intervention group or control arm. Contrast injection with ERC catheter after attempt of bile extraction will be used in both groups. In the control arm, the procedure is terminated after contrast injection. They will be managed using a strictly conservative strategy that avoids biliary interventions unless such intervention is unequivocally mandated by the clinical situation. We foresee that this will be the case only in cholangiosepsis with obstruction which is part of the composite endpoint. Patients in the control arm will be seen every 8 weeks and a blood collection with acquisition of clinical data will be performed. After 6 months, a control MRCP will be performed in both groups in order to evaluate and compare the extent of bile duct damage between the groups. In the intervention group potential endoscopic interventions are as follows: sphincterotomy (V1-4), occlusion cholangiogram (V1-V4), extraction of all removable biliary casts via balloon, brush, basket and/or flushing (V1-V4), dilatation or bougienage of all endoscopically treatable bile duct stenoses (V1-V4), largest size of balloon or bougienage in relation to bile duct size has to be applied (V1-V4). Selective intubation of ductus hepaticus sinister and dexter with visualization and balloon cleaning is preferred (V1-V4). At the end of the procedure, flushing of the left and right biliary system with 20 ml Ringer’s lactate solution in order to flush remnants of contrast medium (V1-V4) and stent placement at physician’s assessment V1-V4 (high-grade stenosis of the bile ducts with insufficient dilatation or bougienage) will be performed. After the ERC, the following items have to be documented: procedure time, the extracted material (stones, cast, sludge and/or pus), largest size of balloon or bougienage if used, the possibly applied stent(s) and the potential use of intra-biliary antibiotics, flushing catheters or nasobiliary drainage (V1-4).

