**Primary estimand:**	
Intercurrent events	Early discontinuation of the study
Strategy	Treatment policy
Population-level summary	A Mantel–Haenszel estimate for the risk difference (experimental minus control group) with center as stratification factor will be used to compare treatment failures in all randomized patients
Estimand description	Superiority of the experimental group on the composite endpoint of death, liver transplantation or cholangiosepsis will be measured using the Mantel–Haenszel estimate for the risk difference irrespectively from the early discontinuation of the study
Imputation/data/censoring rule(s)	Patients who early discontinue the study without assessment of the primary endpoint will be counted as treatment failures
Sensitivity analyses	1)Estimation of the risk difference and the corresponding 95% CI without adjustment for center 2)Estimation of the risk difference and the corresponding 95% CI in a model where patients who early discontinue the study without assessment of the primary endpoint are counted as treatment responders 3)Estimation of the risk difference and the corresponding 95% CI in the per-protocol population

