#### Analyses populations

The primary analysis will be conducted on the ITT-population including all patients that have been randomized. Patients will be analyzed as randomized independently of the performed intervention.

The per-protocol (PP)-population comprises all patients that received the randomized group and were complying with the study-protocol until the end of the observational period and particularly remained in the treatment arm they were allocated to by randomization.

Safety population: In the safety population, all patients are analyzed who are randomized. Patients will be analyzed as treated.

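### The per-protocol set is tied to completing the study with no exemption for endpoint events, so read literally it drops patients who die from an analysis of a composite that includes death

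*Protocol article*

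**What the plan says.** The protocol states the per-protocol rule twice, in different terms.

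- Analysis of the primary endpoint: the population is one "which consists of all patients who complete the study in accordance to the protocol".
- Analyses populations: patients must have received the allocated treatment and been "complying with the study-protocol until the end of the observational period and particularly remained in the treatment arm they were allocated to by randomization".

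Table 3 uses this set for the third of three sensitivity analyses of the primary estimand: "Estimation of the risk difference and the corresponding 95% CI in the per-protocol population". The main analysis does not use it: "The primary analysis will be performed according the intention-to-treat (ITT) principle".

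Three other statements bear on who belongs in the set.

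- The primary endpoint is death, liver transplantation or cholangiosepsis within 6 months, but under Trial design "Study participants will be followed up to 12 months following study inclusion".
- Under Interventions, controls follow a strategy that "avoids biliary interventions unless such intervention is unequivocally mandated by the clinical situation".
- The same section adds: "We foresee that this will be the case only in cholangiosepsis with obstruction which is part of the composite endpoint".

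**The concern.** A patient who dies does not complete the study in the ordinary sense of the words. Death is also one of the three events that the analysis counts. Whether a patient belongs to the set then depends on the outcome being estimated, and the arm with more deaths loses more patients. What remains is a comparison among survivors, which is not the comparison randomization protects.

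The time frame adds to this. If the observational period means the full 12 months, a patient who reaches month 6 without an event and dies in month 9 is also excluded, although the primary outcome was already known.

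At stake is the only one of the three sensitivity analyses that addresses adherence, and the only one named in the running text beside the primary analysis. If it differs from the main result, a reader could not tell whether non-adherence or the exclusion of endpoint patients was the cause. Sites know the allocation, so leaving the classification open also invites decisions made after outcomes are known.

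**Working it through.** **1. The plan's own figure.** Inputs from Sample size: 70% versus 40%, two-sided 5%, power 80%, continuity-corrected chi-square test, 5% drop-out.

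- Uncorrected: n = [1.96·√(2·0.55·0.45) + 0.8416·√(0.7·0.3 + 0.4·0.6)]² / 0.30² = (1.3790 + 0.5646)² / 0.09 = 41.97, so 42 per arm.
- Corrected: (41.97/4)·[1 + √(1 + 4/(41.97·0.30))]² = 48.4, so 49 per arm.
- Drop-out: 49/0.95 = 51.6, so 52 per arm and 104 in total.

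The stated 49, 52 and 104 are reproduced.

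**2. The planned contrast at 52 per arm.** Risk difference 0.40 - 0.70 = -0.30. SE = √(0.7·0.3/52 + 0.4·0.6/52) = 0.093, giving a 95% CI of -0.48 to -0.12.

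**3. Removing a share f of the events.** With event rate p in an arm:

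- patients left = 52·(1 - p·f)
- event rate left = p·(1 - f)/(1 - p·f)

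The documents do not give the split of the composite, so f is an assumption, taken as equal in both arms. Two values can be anchored in Sample size. Survival below 50% within 3–6 months suggests deaths of about 50 in every 70 control events (f = 0.714). Transplant-free survival of 38.9% at 6 months gives 100 - 38.9 = 61.1% death or transplantation (f = 61.1/70 = 0.873). Two smaller shares show the range.

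| Events removed (both arms) | Patients left, control vs ERC | Event rate, control vs ERC | Risk difference (95% CI) | Power |
|---|---|---|---|---|
| none | 52 vs 52 | 70% vs 40% | -0.30 (-0.48 to -0.12) | 88% |
| 25% | 43 vs 47 | 64% vs 33% | -0.30 (-0.50 to -0.11) | 83% |
| 50% | 34 vs 42 | 54% vs 25% | -0.29 (-0.50 to -0.08) | 73% |
| 50/70 (deaths) | 26 vs 37 | 40% vs 16% | -0.24 (-0.46 to -0.02) | 57% |
| 61.1/70 (deaths and transplants) | 20 vs 34 | 23% vs 8% | -0.15 (-0.36 to 0.05) | 36% |

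Worked line for deaths. Control: 52·(1 - 0.50) = 26 patients, rate 0.20/0.50 = 0.40. ERC: 0.40·0.714 = 0.286 die, so 52·0.714 = 37 patients, rate 0.114/0.714 = 0.16. Difference -0.24.

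Intervals are unstratified Wald intervals at expected counts. Power is for the uncorrected test, so the 88% is not comparable with the plan's 80%. The planned Mantel–Haenszel interval stratified by center would differ somewhat.

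**4. What the text settles for each component.**

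- Death: excluded on a literal reading of the completion requirement.
- Transplantation: not settled. Nothing says that it ends participation, and Table 2 keeps checking endpoint components at the follow-up visits.
- Cholangiosepsis in a control who then has a biliary intervention: not settled by the per-protocol wording. Interventions permits a clinically mandated procedure, but the condition of having remained in the allocated arm could be misread to exclude that patient.

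**The case against.** The best defence is that this is one sensitivity analysis. Superiority is decided only by the intention-to-treat confidence interval, and the protocol nowhere says that the per-protocol result must confirm it. That stands, and it limits the weight of the point.

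A second defence is that observation of a patient ends at death, so someone who dies has complied to the end of the period, and that operational rules belong in an analysis plan that is not shown. This is a possible reading of the statement under Analyses populations. It does not rescue the other statement, which requires completing the study. The protocol has fixed the rule in two places without an exemption, so this is more than a detail left for later.

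A reader might go further and infer that all three components remove patients, and that control cholangiosepsis does so in one arm only. Removing deaths and transplants in both arms (61.1/70 of events) plus all control cholangiosepsis leaves about 16 versus 34 patients with rates of 0% and 8%. The risk difference is then +0.08, a reversed sign. The documents do not support this. A mandated biliary intervention is part of the control strategy as described, so it is not in itself a deviation. It is foreseen only where there is obstruction. No statement makes transplantation a reason to stop. The reversal is a worst case under an unstated rule.

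**Conclusion.** The point holds for deaths, which the literal wording excludes. For transplantation and for permitted biliary interventions in controls, it holds only as an ambiguity to be closed.

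The size depends on the assumed share of events removed and on that share being equal in the two arms. If a quarter to a half of events go, the risk difference barely moves (-0.30 to -0.29) and the loss is mainly in numbers. If deaths are 50/70 of events, it moves to about -0.24. If transplants go as well, it is about -0.15 and the interval includes 0. The survival figures quoted in the protocol point towards the larger shares, but they come from earlier reports and a cohort, not from this trial. If deaths form a different share of events in each arm, the shift would differ from these figures.

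The primary analysis, its decision rule, the type I error and the sample size of 104 are untouched. This is a correction worth making before outcome data are analyzed by arm; it does not threaten the main conclusion.

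**What to change.** Use one per-protocol definition in both Analysis of the primary endpoint and Analyses populations:

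- Assess adherence only up to the first primary-endpoint event or month 6, whichever is earlier.
- Keep patients with death, transplantation or cholangiosepsis in the set, with their event counted.
- State that a biliary intervention in a control patient that the protocol permits is not a deviation. A rule excluding every control with a therapeutic ERC before the first event would contradict Interventions.
- Delete the requirement to complete the study and the requirement to comply to the end of the observational period.

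If no other deviations occur, the set then keeps the planned contrast of 70% versus 40% (-0.30, 95% CI -0.48 to -0.12 at 52 per arm). The cost is wording in two paragraphs, with no new data and no change in sample size.
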